#### Secondary outcomes

The proposed outcomes and evaluation methods for the larger-scale evaluation will include the following:Proposed individual level outcomes:i.Family empowermentii.Parent patient activation and health literacyiii.Parent/carer wellbeingiv.Parent/carer quality of lifev.Parents/carers perceived greatest needs (baseline only) and goals for the intervention (baseline and endpoint)vi.Review of goals achieved (endpoint only)Economic outcomei.Childhood cost calculator (C3): A costing tool for education and early childhood development [43]

The above outcome measures proposed for the larger evaluation will be assessed in the response, completion rates and acceptability during data collection. Table 3 summarises the outcome measures and data collection timing.

**Table 3 Tab3:** Outcome measure and data collection timing for proposed outcomes and evaluation methods for the larger-scale evaluation

Outcome	Outcome measures	Timing			
		Baseline	End of each “Encompass” group	Post-intervention	3-month follow-up
Proposed individual-level outcomes	Family Empowerment Scale (FES)	X		X	X
	Empowerment ladder	X		X	X
	Parent Patient Activation Measure (P-PAM)	X		X	X
	Warwick-Edinburgh Mental Wellbeing Scale (WEMWBS)	X		X	X
	EuroQoL-5D-5-level (EQ-5D-5L)	X		X	X
	Parent/carer greatest needs and goals	X		X	
Economic outcomes	Childhood Cost Calculator (C3)				X
Process outcomes	Fidelity checklist		X		
	Direct observation		X		
	Group register		X		
	Intervention satisfaction survey			X	
	Qualitative semi-structured interviews			X	

### Family empowerment

The Family Empowerment Scale (FES) [44] is a validated 34-item instrument that measures parents’ sense of empowerment across three areas: family, service use and community. It has been used in the ENVISAGE parent workshops [18] and aligns with the goals of the “Encompass” groups which are to empower families to understand their child’s diagnosis and how to navigate health systems. A limitation of this tool is that it has mostly been used with a white, United States (US) population [45].

The Power Ladder Question (PLQ) assesses participants’ perceived sense of power and influence over their life. The survey asks: “Please imagine a nine-step ladder, where on the bottom, the first step, stand people who are completely without rights, and on the highest step, the ninth, stand those who have a lot of power. On which step are you?” [46]. It has been used with diverse groups and allows the participant to choose the domains of power that they value and interpret the question openly [47].

### Healthy literacy and patient activation

Parent patient activation relates to the knowledge, skills, confidence and persistence to manage a child’s health care, particularly those with developmental disorders or disabilities [48–50]. The Parent-Patient Activation Measure (P-PAM) is a validated 13-item tool that measures two factors: “confidence and knowledge” and “action and perseverance” [51]. It has been used in a variety of diverse settings, including low income, non-English-speaking parents [52].

### Parent/carer wellbeing

The Warwick-Edinburgh Mental Wellbeing Scale (WEMWBS) has been widely used to assess wellbeing across a diverse range of public health interventions, populations and settings [53, 54]. The 14-item scale WEMWBS will be used with five response categories that are summed up to provide a single score [55].

### Parent/carer quality of life

The EuroQoL 5-dimension questionnaire is a validated and widely used tool that measures generic quality of life. It has one question for each of the five dimensions (mobility, self-care, usual activities, pain/discomfort and anxiety/depression) with five response options [56].

### Parent/carer needs and goals

A questionnaire has been adapted from previous evaluations of Ubuntu interventions [57]. It has two questions and asks parents/carers what their three biggest issues are that they face in everyday life and what their two main goals are for attending the group.

### Qualitative data

Qualitative data collection in the form of semi-structured interviews will take place with 4–6 purposefully sampled parent/carer participants per group to reflect a variety of perspectives (e.g. low/high attendance, severity of their child’s difficulties, age or gender), along with both facilitators (*n* = 2) and key NHS partners (*n* = 2–4). As qualitative research is iterative, the semi-structured interview questions will be open-ended, and the direction cannot be fully anticipated. However, the topic guides indicate the broad topics that will be discussed with each participant. The guides were developed based on the TDF and the Context Compass Framework, along with input from the PPI and advisory groups.

Semi-structured interviews with parents/carers will explore their satisfaction with and perceived impact of the intervention, their level of participation in the community, confidence levels, experiences of discrimination and the impact of their child’s disability. They will also be asked their opinions about the data collection tools and outcome measures that were used.

The topic guides for the facilitator interviews were developed based on previous evaluations of the Ubuntu interventions, the Theoretical Domains Framework and the Context Compass Framework. These interviews aim to explore the facilitators’ experiences of how the intervention ran, perceived impacts of the intervention and how it may be integrated into existing services.

Semi-structured interviews with key NHS partners from the local health and care system will explore the acceptability of incorporating the “Encompass” intervention into current services and pathways, potential facilitators and barriers, theoretical feasibility and cost-effectiveness. They will also be asked their views on outcomes that should be measured in a larger-scale evaluation.

### Background demographic data

Basic background demographic data will be collected at the first groups from the parents/carers. This will be combined with background data accessed from the children’s medical records about their diagnosis and interactions with different health services.

#### Data management and access

Data will be managed and overseen by City, University of London. Semi-structured interviews will be audio-recorded, and either transcribed verbatim by a professional transcriber or transcribed through Teams if it took place online. Transcripts will be pseudo-anonymised so that no individual or organisation can be identified from the data.

All digital recordings, anonymised transcripts and other person-identifying research data will be stored in password-protected files on secure servers at City, University of London. Only the immediate research team will have access to these files.

Digital recordings will be destroyed at the end of the study. Anonymised research data will be held on City, University of London servers for 10 years.

A password-protected database of participant contact details will be stored separately from the anonymised research data. This will be held on City, University of London secure servers, and only the research team will have access to these files. This database will be erased at the end of the study.

### Sample size

The sample size of the study was generated based on a variety of literature and methods. Simple confidence interval calculations were used for the feasibility estimates research questions and qualitative justifications for the acceptability research questions.

As the objectives of the feasibility study relate to estimating a rate (i.e. the proportion of people) of those who completed follow-up questionnaires and attended the groups, it is suggested that confidence intervals may be calculated by relating the proposed sample size to the width of the confidence interval for the rate, using the following equation with *P* being the proportion one expects to see and *n* the intended sample size [58]:$$1.96 \times \surd (P \times (1-P)/n)$$

The standard error of a proportion depends on the value of the proportion itself, reaching its largest value when the proportion equals 0.50 [58]. The table below displays the width of confidence intervals across reference sample sizes for two values of proportion (Table 4):An estimation of the follow-up response rate questionnaires being 70%As estimation of group attendance (attending > 6 out of 10 modules) of 80%

**Table 4 Tab4:** Width of confidence intervals across reference sample sizes for two values of proportion (completion of follow-up questionnaires and group attendance)

*n*	Group configuration		*P*	CI_95_
12	Two groups of six each	Follow-up	0.70	0.26
		Attendance	0.80	0.23
16	Two groups of eight each	Follow-up	0.70	0.22
		Attendance	0.80	0.20
20	Two groups of 10 each or 3 groups of 6 or 7 each	Follow-up	0.70	0.20
		Attendance	0.80	0.18
24	Three groups of eight each	Follow-up	0.70	0.18
		Attendance	0.80	0.16
30	Three groups of 10 each	Follow-up	0.70	0.16
		Attendance	0.80	0.14

For a follow-up response rate of 70% in the feasibility study of 12 participants, we can be 95% confident that this estimate is accurate within + / − 26%. When the sample size is increased to 20 participants, the error in estimation is reduced to 20 percentage points. If increased to 24 participants, this is only slightly reduced to + / − 18%. An increase to 30 participants results in a marginal reduction to + / − 16%.

The above calculations relate to the feasibility rate estimates and suggest that a sample of 20 may be adequate.

As this is a mixed-methods study, qualitative data will be collected around the acceptability of delivering and receiving the intervention. Information power [59] has been proposed as a tool to guide sample size in qualitative research. It suggests that a sample with greater information power requires a lower *n* and vice versa. The model proposes that certain considerations will require either the least amount or a larger number of participants. The aim of the qualitative data collection is narrow (exploring the acceptability of delivering and receiving the intervention), and the researcher ([name]) is confident in her abilities to conduct interviews with strong dialogue due to her background as an occupational therapist and recent experience in conducting a similar qualitative study. The theoretical background is strong as there have been multiple studies globally that have explored the same topic, albeit in different contexts. Participants for the qualitative data collection are required to have highly specific characteristics that have not been previously described, for example residing in a high-income country with ethnic and linguistic diversity. These characteristics of aim, specificity, dialogue and theory enhance information power resulting in fewer participants required. Based on the above, a sample size consisting of the facilitators (*n* = 2), parents/carer (*n* = 8 to 12) and key NHS partners involved in local health and care system commissioning and management (*n* = 2 to 4) may be sufficient for the qualitative study.

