**Methods and analysis:**

We will conduct a mixed-methods pilot feasibility study to determine the feasibility and acceptability of delivering and evaluating “Encompass” with parents/carers of children under 5 years with complex neurodisability in the UK. We aim to recruit 20 parents/carers of children from two NHS trusts in England serving urban areas where there is high social deprivation and ethnic diversity. Recruited parents/carers will attend the 10-modular, participatory group programme over a 6-month period. Groups will be facilitated by a trained allied health professional and an “expert parent” with lived experience. The primary outcomes of interest are the feasibility of delivering and evaluating the programme (recruitment, retention rates, acceptability as perceived by the parents/carers, facilitators and wider key NHS partners), intervention fidelity and participant adherence. Results will be collectively assessed against traffic light criteria. Pre-, post- and follow-up data collection questionnaires will include the Family Empowerment Scale (FES), the Power Ladder Question, the Parent Patient Activation Measure (P-PAM), Warwick-Edinburgh Mental Wellbeing Scale (WEMWBS), EuroQoL-5D-5-level (EQ-5D-5L) and parent/carer greatest needs and goals questionnaire. Post-intervention semi-structured interviews will be conducted with parents/carers, facilitators and key NHS partners.

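### Table 4 labels half-widths as confidence interval widths, and its margins for n = 20 take no account of the groups

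*Protocol article*

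**What the plan says.** The abstract sets the target: "We aim to recruit 20 parents/carers of children from two NHS trusts in England". The Sample size section justifies it by "relating the proposed sample size to the width of the confidence interval for the rate", and gives the formula 1.96 × √(P × (1−P)/n). Table 4 is then introduced as showing the "width of confidence intervals across reference sample sizes for two values of proportion", and its caption uses the same words. The two planning values are "An estimation of the follow-up response rate questionnaires being 70" per cent and "As estimation of group attendance (attending > 6 out of 10 modules) of 80" per cent.

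At n = 20 the table prints 0.20 for follow-up and 0.18 for attendance, with the configuration "Two groups of 10 each or 3 groups of 6 or 7 each".

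The paragraph below the table takes the follow-up column only. For n = 12 it says "we can be 95% confident that this estimate is accurate within" plus or minus 26%, and it goes on to an error of 20 percentage points at n = 20, plus or minus 18% at n = 24 and plus or minus 16% at n = 30. The section concludes that the calculations "suggest that a sample of 20 may be adequate".

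**The concern.** The section gives one quantity two meanings. The two lead-in sentences and the caption call it a width; the paragraph after the table treats it as a margin on either side of the estimate. Only one can be right, and they differ by a factor of two. A reader who goes to the table alone, or who wants the attendance figures, has only the *width* label to go by.

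The second issue is what the formula leaves out. Table 4 has a column for group configuration, but nothing in the formula depends on it: two groups of 10 and three groups of 6 or 7 share one row and one margin. Parents meet as a group, at a shared venue and time and with the same peers, so whether one attends may be related to whether another does. If so, 20 parents carry less information than 20 independent people.

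This table is the only quantitative support for n = 20, because the remainder of the sample size justification concerns the interviews. What is at stake is how precisely readers, and the planners of the larger evaluation, believe the feasibility rates will be known.

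**Working it through.** **Inputs.** From the Sample size section: the formula, P = 0.70 and 0.80, and n = 12 to 30. The 95% level is two-sided, with multiplier 1.96. Groups at n = 20: two of 10 (the Methods section also says two groups) or three of 6 or 7. No ICC is given, so 0.01 to 0.10 is an assumed range.

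**Step 1: reproduce Table 4.** Half-width = 1.96 × √(P(1−P)/n).

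| n | P = 0.70, computed | printed | P = 0.80, computed | printed |
|---|---|---|---|---|
| 12 | 0.259 | 0.26 | 0.226 | 0.23 |
| 16 | 0.224 | 0.22 | 0.196 | 0.20 |
| 20 | 0.201 | 0.20 | 0.175 | 0.18 |
| 24 | 0.183 | 0.18 | 0.160 | 0.16 |
| 30 | 0.164 | 0.16 | 0.143 | 0.14 |

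All ten cells agree to two decimals, and all are half-widths. The arithmetic is right and the name is wrong.

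**Step 2: full widths at n = 20.** 2 × 0.2008 = 0.402 for follow-up (0.499 to 0.901) and 2 × 0.1753 = 0.351 for attendance (0.625 to 0.975).

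**Step 3: does the large-sample formula matter at n = 20?**

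| Method | 14/20 | width | 16/20 | width |
|---|---|---|---|---|
| Wald | 0.499 to 0.901 | 0.402 | 0.625 to 0.975 | 0.351 |
| Wilson | 0.481 to 0.855 | 0.374 | 0.584 to 0.919 | 0.335 |
| Exact (Clopper-Pearson) | 0.457 to 0.881 | 0.424 | 0.563 to 0.943 | 0.379 |

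Widths differ from Wald by about 0.02 to 0.03, Wilson being narrower and exact wider. The limits sit lower under both alternatives. At n = 12 and P = 0.80 the Wald upper limit is 0.80 + 0.226 = 1.026, which is impossible, but that sample size was not chosen.

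**Step 4: allow for the groups.** Design effect = 1 + (m − 1) × ICC; half-width = 1.96 × √(P(1−P) × design effect / 20); effective n = 20 / design effect. With m = 10:

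| Assumed ICC | Design effect | Effective n | Follow-up half-width | Attendance half-width |
|---|---|---|---|---|
| 0 (as in the protocol) | 1.00 | 20 | 0.201 | 0.175 |
| 0.01 | 1.09 | 18.3 | 0.210 | 0.183 |
| 0.05 | 1.45 | 13.8 | 0.242 | 0.211 |
| 0.10 | 1.90 | 10.5 | 0.277 | 0.242 |

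With three groups (mean size 20/3 = 6.67) and the same ICC range, the half-widths are 0.206 to 0.251 for follow-up and 0.180 to 0.219 for attendance. The two configurations that share a row in Table 4 therefore differ in precision unless the ICC is zero.

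**The case against.** The strongest reply is that the plan reads its own numbers correctly where it matters. The printed formula is recognisably a margin of error, the paragraph below the table uses plus or minus, and the statement about n = 20 follows that reading. This stands. A reader might infer from the caption that the stated precision is twice too good throughout; the document does not support that, because no doubling enters the reasoning about follow-up.

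A reader might also blame the large-sample formula for the factor of two, or argue that poor Wald coverage undermines n = 20. Neither holds. The factor of two comes from the label alone, as Step 3 shows. Plug-in Wald coverage falls well short at some sizes not chosen (87.6% at n = 12, P = 0.70), but at n = 20 it is 94.7% for P = 0.70 and 92.1% for P = 0.80. The plan's own claim is about how close the estimate should fall to the expected proportion. By binomial enumeration, assuming independence, the estimate at n = 20 lies within the printed margin with probability 97.5% (P = 0.70) and 95.6% (P = 0.80).

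On grouping, it is fair to say that the ICC is the reviewer's assumption, and that the two facilitators appear to be one pair serving all groups, which would add no variation between groups. Venue, timing and peers remain as possible sources. Finally, the traffic-light criteria are applied to observed rates, so these margins enter no decision rule. That limits the consequence, but the table remains mislabelled and its independence assumption unstated.

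**Conclusion.** The concern holds in a limited form. The caption of Table 4 and the two sentences leading into it name a half-width as a width; at n = 20 the full widths are about 0.40 and 0.35, not 0.20 and 0.18. The text below the table is right for follow-up and silent on attendance.

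The margins also assume independent parents, which makes them best-case if attendance or response is positively correlated within groups. The size of that loss cannot be derived from the document. With two groups of 10 and an assumed ICC of 0.01 to 0.10, the attendance half-width is 0.18 to 0.24 and the follow-up half-width 0.21 to 0.28. At the bottom of that range the change is negligible; at the top it is an increase of about 38% (√1.90 = 1.378).

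This is a wrongly labelled figure and an unstated assumption in the sample size justification. It does not show that 20 is the wrong number.

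**What to change.** 1. Rename the Table 4 column and caption *half-width (margin of error) of the 95% confidence interval*, and change the two lead-in sentences to match. Alternatively print lower and upper limits, preferably Wilson or exact; the exact limits at n = 20 are 46% to 88% for 14/20 and 56% to 94% for 16/20.
2. Say in words what the attendance figure means, as is already done for follow-up.
3. State that the figures assume parents within a group are independent, and show the half-width at n = 20 over an assumed ICC range such as 0.01 to 0.10, separately for two and for three groups.
4. Restate the conclusion on that basis, for example that 20 parents in two groups of 10 give a margin of roughly 20 to 28 percentage points around a 70% follow-up rate, and 18 to 24 around 80% attendance, for an ICC between 0 and 0.10.

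The cost is one recalculated table and a few sentences. The sample size, conduct and progression criteria are untouched. The only downside is a slightly less favourable statement of precision.

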### Data analysis

Recruitment rates, completion rates for baseline and follow-up outcomes and attendance rates will be assessed against the traffic light criteria.

Quantitative data, such as the Family Empowerment Scale and satisfaction survey, will be descriptively summarised using mean and standard deviation for continuous variables and number with percentages for categorical variables.

Qualitative data will be audio-recorded and transcribed, and NVivo software will be used to manage and organise the data. Data will be analysed thematically [60] both deductively and inductively. Analysis will be guided by the TDF and the Context Compass Framework described previously. By developing the topic guides using these frameworks, it ensures that key contributors to feasibility are explored. Thus, data that will be coded and analysed deductively within the TDF and Context Compass frameworks to develop qualitative themes that likely to map to the framework domains. However, it is also likely that other themes may arise from the data that do not map to the domains of these frameworks (inductive analysis).

During data synthesis, the research team will aim to look for congruence and incongruence between qualitative and quantitative findings, as well as attempting to use qualitative data to clarify quantitative findings.

### Ethics

Ethical approval has been obtained from the Health Research Authority (ref. 23/EM/0213). Key considerations include the researchers having a clear understanding of the informed consent procedures, with it being emphasised that declining to participate or withdrawing from the study will not affect a child’s healthcare in any way. Appropriate procedures are in place for safeguarding if any participant discloses inappropriate clinical practice or indicates that they or their family may be at risk of harm at any time over the course of this research. Participant confidentiality and data protection have been considered throughout. All personal data will be collected, stored and processed in accordance with the Data Protection Act 2018 and General Data Protection Regulation. Participants will be informed of their rights to confidentiality and the rights of others; however, limits to confidentiality will also be explained; for example, in the case where a parent or child may be at risk of harm, the research team may need to notify external parties to protect the safety of parents/children.

There is a risk of parents/carers feeling emotional distress in the group setting. This phase of the study includes parents/carers with young children who are either newly diagnosed or in the process of being diagnosed with a complex neurodisability. At this stage, parents/carers may be experiencing difficulties with their mental health [4] and feelings of denial, anxiety and worries about the future, as was seen in the Encompass 1 study. Parents/carers with newly diagnosed children with CP often find comfort in a group setting; however, it can at times be too emotionally difficult to see others within the group, particularly those with more severe physical difficulties [61]. Facilitators of the groups will be experienced physiotherapists or occupational therapists, as well as other parents with lived experience, who will receive training about supporting parents/carers’ needs around the time of diagnosis. Signposting will be provided for further psychological support if required.

